### Sample size

The sample size for the household surveys will be calculated using the assumption that that the roll out of proven and effective interventions within existing health delivery platforms for MNCH will lead to significant reduction in PNM rate (20% compared with baseline) and at least 30% reduction in diarrhoea and pneumonia case fatality rates in the target districts for the proposed UeN scale-up initiative. PNM will be used as the primary outcome for all sample size projections. A stratified two-stage cluster sampling approach will be used to calculate sample size. Moreover, it is important to power the study to provide a detectable difference between the maternal and newborn health group, and the CH group. We will use a before and after design for sample size calculation. For MNH districts, assuming a 20% reduction in the PNM from the baseline PNM of 75 per 1000 live births (Pakistan Demographic Health Survey 2012 to 2013 for rural Pakistan)^30^ with a power of 80% to detect the difference in the PNM between baseline, and the endline household survey, a type I error of 5%, design effect of 1.515 and an annual attrition of 10% per year, at least 19 582 households will be enrolled in the survey. For CH intervention districts, assuming a 30% reduction in the post neonatal death (PND) rate of 19/1000 live births at baseline (Pakistan Demographic Health Survey 2012 to 2013 for rural Pakistan) with a power of 80% to detect the difference in the PND between baseline and the endline household survey, a type I error of 5%, design effect of 1.388 and an annual attrition of 10% per year, at least 19 210 households have to be enrolled in the survey.

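### The MNH and CH household totals do not both follow from their stated inputs: CH needs about 1.6 times the births of MNH but is given 2% fewer households

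*Protocol article*

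**What the plan says.** All of this is in the protocol article, Methods and analysis, Sample size.

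- Both groups are sized the same way: "We will use a before and after design for sample size calculation".
- MNH districts: "assuming a 20% reduction in the PNM from the baseline PNM of 75 per 1000 live births", "with a power of 80% to detect the difference in the PNM between baseline, and the endline household survey", with "a type I error of 5%, design effect of 1.515 and an annual attrition of 10% per year". The result is "at least 19 582 households will be enrolled in the survey".
- CH districts: "assuming a 30% reduction in the post neonatal death (PND) rate of 19/1000 live births at baseline", "with a power of 80% to detect the difference in the PND between baseline and the endline household survey", with "a type I error of 5%, design effect of 1.388 and an annual attrition of 10% per year". The result is at least 19,210 households.

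Power, type I error and yearly attrition are therefore the same in both groups. Only the baseline rate, the relative reduction and the design effect differ. The rates are per 1000 live births and the totals are households. The section gives no births per household, recall window, sidedness or number of attrition years, and does not say whether a total is per survey or for both surveys together.

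**The concern.** The CH outcome is about four times rarer than the MNH outcome (19 against 75 per 1000). The larger relative reduction and slightly smaller design effect in CH make up only part of that, so CH should need clearly more births. It is given slightly fewer households.

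The missing conversion from births to households is not itself the complaint, since an article may leave that to the full protocol. The complaint is that two printed results conflict with printed inputs, because anything the two groups share cancels from the ratio. The post-neonatal death calculation is also the only sizing offered for the child health hypothesis. If the two totals cannot both be right, a reader cannot rely on 80% power in both groups.

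**Working it through.** **Inputs (Sample size section).** MNH: p1 = 0.075, p2 = 0.075 × 0.80 = 0.060, design effect 1.515. CH: p1 = 0.019, p2 = 0.019 × 0.70 = 0.0133, design effect 1.388. Both: power 80% (z = 0.8416) and type I error 5% (two-sided z = 1.9600; sidedness is my assumption and is varied below).

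**Step 1. Births per survey.** With p̄ the mean of p1 and p2,

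n = [1.9600·√(2p̄(1−p̄)) + 0.8416·√(p1(1−p1) + p2(1−p2))]² / (p1−p2)²

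- MNH: (1.9600 × 0.35481 + 0.8416 × 0.35465)² / 0.015² gives 4,391. Times 1.515 = 6,652.
- CH: (1.9600 × 0.17827 + 0.8416 × 0.17822)² / 0.0057² gives 7,676. Times 1.388 = 10,654.

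Required CH/MNH ratio: 10,654 / 6,652 = 1.60. Stated household ratio: 19,210 / 19,582 = 0.98.

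**Step 2. Can the stated totals be reproduced?** Variants tried were one- and two-sided tests, with and without continuity correction, one survey or two, and a range of attrition allowances. None gives both totals within 3%. Each can be approached alone, by a different rule:

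| Rule (one birth per household) | MNH | CH |
|---|---|---|
| Stated | 19,582 | 19,210 |
| Two-sided, continuity correction, both surveys, divided by 0.7 | 19,578 | 31,817 |
| Two-sided, continuity correction, one survey, divided by 0.9⁵ | 11,605 | 18,859 |

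These rows do not show which rule was used. They show only that a rule fitting one total misses the other.

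**Step 3. How firm is the ratio?** Across sidedness and continuity correction, applied alike to both groups, it is 1.60 to 1.63. A shared attrition factor, number of surveys or births per household cancels. Even a deliberately mismatched pair (CH one-sided and uncorrected, MNH two-sided and corrected) gives 1.22, still above 0.98.

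**Step 4. What would reconcile the totals?** Households per required birth are 19,582 / 6,652 = 2.94 in MNH and 19,210 / 10,654 = 1.80 in CH. CH households would have to yield 2.94 / 1.80 = 1.63 times as many births. Table 1 gives under-5 shares of 520,990 / 4,926,403 = 10.6% in MNH districts. For CH districts the share is 627,144 / 6,180,338 = 10.1% without Rahim Yar Khan, whose entry is garbled, or 11.4% if that entry is read as 625,820. The CH/MNH ratio of these shares is 0.96 to 1.08, far from 1.63.

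**Step 5. Power if the MNH total is right.** At the MNH yield, 19,210 households give 19,210 / 2.94 ≈ 6,526 births per survey, or 6,526 / 1.388 = 4,702 effective births. Then

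power = Φ[(0.0057 − 1.9600 × 0.17827/√4,702) / (0.17822/√4,702)] = Φ(0.23) = 59%.

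| CH/MNH births-per-household ratio | 1.0 | 1.1 | 1.25 | 1.5 | 1.63 |
|---|---|---|---|---|---|
| CH power | 59% | 63% | 69% | 77% | 80% |

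At equal yield, CH would need 19,582 × 1.6016 ≈ 31,360 households.

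**Step 6. Power if the CH total is right.** At the CH yield, 19,582 households give 19,582 / 1.80 ≈ 10,861 births, or 10,861 / 1.515 = 7,169 effective births, and MNH power is Φ(1.62) = 95%. MNH would need only about 11,990 households.

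**The case against.** The strongest case against is that births per household is not given and need not be equal. Perinatal death is settled within a week of birth, whereas post-neonatal death comes later, so the two outcomes could use different recall windows and different yields. Table 1 speaks to population structure, not to recall. This stands as a possibility. But it has to produce a ratio of about 1.63, no group-specific conversion is stated, and the article describes one set of household surveys on one schedule.

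A reader might infer that the CH group is left at 59% power, or that any shortfall must fall on CH. The documents do not support that. The 59% requires both that 19,582 is the correct total and that yields are equal, and neither is stated. The opposite reading is open. Suppose 19,210 is per survey, with one birth per household and five years of 10% attrition. Then 19,210 × 0.9⁵ = 11,343 births per survey, above the 10,654 needed. CH has about 82% power and MNH about 96%. On that reading no group is underpowered and the MNH total is simply larger than its stated inputs require.

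A reader might also infer that an attrition allowance is misplaced because no household is followed. The article describes surveys at three time points and does not say whether households are revisited, so that is not established. The ratio does not depend on it.

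**Conclusion.** The point holds as an internal inconsistency. On the stated rates, design effects, power, type I error and attrition, CH needs 1.60 to 1.63 times the births of MNH, while the totals stand at 0.98. At least one total, or the 80% attached to it, is wrong unless CH households are assumed to yield about 1.63 times as many births. That assumption is not stated, and the Table 1 under-5 shares lend it no support.

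Which total is wrong cannot be told from the article. With MNH taken as right, CH power runs from about 59% at equal yields to 80% at a yield ratio of 1.63. With CH taken as right and yields equal, CH has its 80% and MNH about 95%. The inconsistency itself rests only on the two groups sharing one rule. The power figures rest in addition on which total is taken as correct and on the yield ratio, and should be reported only with those conditions.

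**What to change.** Recompute both totals with one stated rule that gives:

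- births per household in the recall window for each outcome, with the reason if these differ between groups;
- whether each total is per survey or over both surveys;
- the attrition or non-response allowance and the number of years it covers;
- the sidedness of the test.

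Then either correct whichever total is wrong, or keep the planned households and restate the power each group actually has. Do not write 59% for CH into the protocol unless the recalculation yields it. If a group-specific conversion was used, stating it with its source would settle the point.

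The cost is a recalculation and a few sentences. Keeping the planned households and restating power costs nothing in the field. Enlarging a sample would add fieldwork, but only if the recalculation shows a real shortfall and the sponsor chooses to make it up.

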### Intervention packages and implementation strategies

An integrated intervention package, that has shown to be relevant, feasible and effective was designed thematically (figure 4) and will be delivered at scale in the target districts. Group 1: Maternal Health: These four districts (Badin, Sanghar, Lasbela and Nasirabad) will receive core MNH interventions as included in global recommendations for maternal health (Helping Mothers Survive)^31^ and newborns (Helping Babies Survive)^32^ consisting of three modules: Helping Babies Breathe, Essential Care for Every Baby and Essential Care for Small Babies. We stratified intervention delivery into three sub-groups focussed separately on maternal health (one district: Sanghar); newborn health (one district: Nasirabad); and combined MNH (two districts: Lasbela and Badin). This stratification was undertaken to independently evaluate the relative impact of theme-specific interventions on key MNH and mortality outcome indicators; that is, akin to a three-arm trial design.

**Figure 4 F4:**
[figure not shown]
Schema of intervention packages for the implementation of maternal and newborn interventions in Pakistan. AKU, Aga Khan University; ARI, acute respiratory infection; CHW, community health worker; LHW, lady health worker; ORS, oral rehydration salts; WASH, Water, Sanitation and Hygiene Education.

Group 2: Child Health: These four districts (Qambar Shahdadkot, Muzaffargarh, Rahim Yar Khan and Jafferabad) representing three provinces will receive CH interventions focussing on the implementation of the Global Action Plan for Pneumonia and Diarrhoea (GAPPD).^33^

Details on UeN intervention approaches packages are displayed in figure 1 and are discussed below by each of the five objectives.

### Objective 1: improve quality of MNCH care

#### Activity 1.1. development of training material and job AIDS

UeN will adopt and contextualise development of training material and job aids in accordance with global and national guidelines to build provider and health worker knowledge, skills and practices. The project team along with experts from the academia and government programmes will develop training packages (including trainer and learner materials, as well as supplemental job aids and guidance) for LHWs and for public and private HCPs.

For private HCPs, 14 modules for on-site learning using academic detailing to refresh the private providers’ knowledge will be developed.

#### Activity 1.2. capacity building

UeN will employ a mix of capacity-building activities to address both outreach workers’ and public sector HCPs’ performance and confidence in achieving quality standards. Training content will be based on the district’s theme. Topics to be covered in the training are listed in figure 4.

Outreach health workers training: LHWs

The LHWs’ skills will be strengthened to promote healthy MNCH practices and behaviours at community-level and will be trained to adhere to care management protocols and use new commodities and technology which includes chlorhexidine, amoxicillin dispersible tablets (dt), zinc dt, low-osmolality ORS, respiratory counters and so on. The LHW training will be based on low-dose high-frequency model.^19 24^

Facility-based: training for providers at primary level and secondary level public health facility

Training for public sector HCPs will be group-based where participants will gather in a public healthcare facility for a competency-based learning activity.

#### Activity 1.3. private sector engagement

Private sector HCPs will be engaged through academic detailing, where individual health providers from private sector (or a facility-based team of providers) will participate in a structured learning activity at their facility. Topics on key areas of MNCH service delivery will be covered.

Initial interaction will be followed by facility-based coaching and mentoring.

#### Activity 1.4. sustained key commodities and supplies by increasing efficiency of the supply chain for essential commodities at community and facility level

Stock Outs of MNCH commodities is a major bottleneck in delivering quality services within the health system.^34^ LHWs, primary level and secondary level healthcare facilities in the target districts will be equipped with essential drugs and equipment to provide quality services through engaging officials of the department of health and other stakeholders. The commodities and supplies will be ensured according to district themes such as for MNH districts, clean delivery kit will be provided to LHWs serving in MNH districts.

For the four MNH districts, clean delivery kits will be provided by Aga Khan University (AKU). For the CH districts, supplies of amoxicillin dt (250 mg), zinc dt, ARI timer and pulse oximeter will be provided by UNICEF in three districts of Punjab and Sindh province; however, since the current UNICEF programme does not cover provision of commodities to Balochistan, AKU will supply the commodities to the CH district in Balochistan.

### Objective 2: improve access to and uptake of MNCH services and practices

#### Activity 2.1. demand generation

Improve uptake of healthy practices at household level through community mobilisation

Through community mobilisation activities, the community will be informed by LHWs about danger signs during pregnancy, child birth, infancy and childhood. The importance of early referral by LHWs to health facilities for prevention of morbidity and mortality will be the focus of community mobilisation activities.

Community engagement through revitalisation/creation of women support groups/ village health committees

LHWs will be trained to revitalise and create where required self-help groups, village health committees and women support groups to discuss MNCH issues. These groups are expected to help women adopt healthy MNCH practices.

### Activity 2.2: expanding the coverage to underserved areas

In the current public health outreach system, LHWs provide services at the household level. However, only 50% to 60% of the rural districts are covered by LHWs.^35^ To serve the geographic areas for which LHWs are not appointed, CHWs will be hired and trained on technical MNCH content, registration, community support group methodology and village health committee formation. Around 100 per district will be deployed. CHWs will be selected on the lower education qualification such as primary education or lower as compared with LHWs who are minimum middle pass. The CHW training will consist of lectures, interactive discussions and role-plays to develop the skills needed to perform their roles. The duration of the training will be 2 weeks, twice in the first year and then a refresher training every year. CHWs will only be recruited and deployed in districts that have maternal, newborn or combined component due to current scope of community health worker programmes.

### Objective 3: promote use of data for decision-making

In Pakistan, there are two main sources of data for decision-making the District Health Information System (DHIS) and the LHW-Management Information System (MIS) for health facility and community level information, respectively. The private sector HCPs do not share routine service delivery data in the DHIS. To promote data use, UeN’s objective is to target all three data sources. Initially, a gaps analysis will be conducted to identify the weaknesses in the system

#### Activity 3.1. improving public health facility-related information system, that is, DHIS

The routine service delivery data of both primary level and secondary level health facilities is managed through DHIS system. The DHIS collects data on the 18 priority diseases, availability of drugs, service usage and human resource of health facilities. Data from each district is discussed in the quarterly district level meetings. However, there is poor compliance with the source registers which is the main source of information. As the data quality is poor and questionable, it cannot guide decision-making.^36^ To improve understanding and importance of collecting data, HCPs of public health facilities will be trained on collection, recording and reporting of the data for DHIS.

For better compliance with source register and data quality, the project team will collect data from source registers on 40 key MNCH indicators every month. Data for these indicators will also be extracted from DHIS monthly reports from the online available dashboard. Values for the indicators from both source register and DHIS dashboard will be compared to assess data completeness and quality.^27^ Monthly feedback report on data quality and completeness will be shared with the managers of health facilities and district managers. Furthermore, quarterly feedback report will be provided about the data quality and summary measures of key MNCH indicators in the district level management meetings.

#### Activity 3.2 improving community-based health information system, that is, LHW-MIS

The LHW is affiliated with a primary health facility and has a catchment population of 1000 and maintains their records; for example, number of married couples, pregnant women, under-5 children and service provision on source registers provided by the LHW programme.^35^ The information collected from the community level is compiled into a monthly report and shared with the lady health supervisor (LHS) and then relayed to the district coordinator for the LHW programme. However, the data quality is not monitored regularly and data use for decision-making is minimal. To improve the data quality, the LHS and LHWs will be trained on the importance of accurate data recording and reporting. Furthermore, 10 LHWs will be randomly selected from their reporting health facility every month; data from their source registers will be collected on 29 MNCH-related indicators on an Android application.

Values for the indicators from both source register and LHW-MIS dashboard will be compared to assess data completeness and quality. Monthly feedback reports will be shared with LHS and LHWs. Furthermore, quarterly feedback report about the data quality and summary of key MNCH indicators will be shared in the district level meetings.

#### Activity 3.3. establishing private providers—MIS

A private provider MIS will be established. Routine data collection registers similar to the DHIS source registers with indicators according to the district themes will be developed and distributed to the private providers. Private providers will be encouraged to record data. The project team will collect data on monthly visits from the health facility. This will enable the capture of MNCH-related morbidities and mortalities which are otherwise lost due to non-reporting.

### Monitoring and impact evaluation

UeN scale-up will undertake rigorous monitoring and evaluation of core activities to ensure project progress and achievement of desired goals. Specific activities are detailed below:

**Household surveys**

Household surveys will be conducted at three time points, baseline, at approximate mid-line when the interventions have been implemented at scale for at least 18 to 24 months, and at the end of the project (towards the end of year 5). The surveys will collect information to assess the impact of the interventions on primary outcome and secondary outcome indicators (listed in table 2).

**Table 2 T2:** List of primary and secondary outcomes

Outcomes	Definition
Primary outcomes	
Perinatal mortality rate	The number of stillbirths and deaths in the first week of life per 1000 total births
Diarrhoea case fatality	Per cent deaths among under-5 children due to diarrhoea
Pneumonia case fatality	Per cent deaths among under-5 children due to pneumonia
Secondary outcomes	
Maternal and newborn health	
Contraceptive use	Per cent of mothers aged 15 to 49 who are using modern contraceptive method
Antenatal care coverage	Per cent of mothers aged 15 to 49 who received antenatal care ≥4 times during pregnancy with their youngest living child aged <6 months
Tetanus toxoid coverage	Per cent of mothers aged 15 to 49 who received ≥2 doses of tetanus toxoid during pregnancy with their youngest living child
Skilled birth attendant at time of delivery	Per cent of mothers aged 15 to 49 whose youngest living child was delivered by skilled health personnel
Institutional delivery	Per cent of mothers aged 15 to 49 whose youngest living child was delivered in a health facility
Postnatal care coverage	Per cent of mothers aged 15 to 49 who received postnatal care (for self or for infant) within 3 days of birth
Early initiation of breastfeeding	Per cent of mothers aged 15 to 49 whose youngest living child was breastfed within 1 hour of birth
Exclusive breastfeeding	Per cent of mothers aged 15 to 49 whose youngest living child was exclusively breastfed
Vaccination coverage among under-5 children	Per cent of mothers aged 15 to 49 whose youngest living child received ≥3 doses of diphtheria, pertussis and tetanus/pentavalent vaccine when aged 12 to 23 months
	Per cent of mothers aged 15 to 49 whose youngest living child received ≥1 dose of measles vaccine when aged 12 to 23 months
	Per cent of mothers aged 15 to 49 whose youngest living child was fully immunised
Care-seeking for diarrhoea among under-5 children	Per cent of mothers aged 15 to 49 whose youngest living child with diarrhoea in the previous 2 weeks received oral rehydration salts and zinc
Care-seeking for pneumonia among under-5 children	Per cent of mothers aged 15 to 49 whose youngest living child with pneumonia-like symptoms in the previous 2 weeks was taken to an appropriate health provider and received antibiotics
Capacity building	Number of healthcare providers trained per 10 000 population
	Number of LHWs trained per 10 000 population

LHW, lady health worker.

